#### Follow-Up

Participants will be followed-up on three occasions: at three, six and 12 months (Table 2). At each follow-up visit, they will be interviewed using a structured questionnaire. They will have blood drawn for the following tests: viral load (at baseline and 12-month follow-up); CD4-T cell count (at each follow-up point); and alcohol biomarker PEth (at each follow-up point). Compensation will be provided to participants in all arms in the form of shopping vouchers for completion of the follow-up assessments.

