Given the repeated measures design, the main statistical analysis will involve repeated analysis of variance and analysis of covariance, using pre-treatment means and post-treatment means; or two-sample t-tests or chi-squared tests at the patient level data. The hypothesis that alcohol reduction will increase adherence will be tested via a repeated-measures Analysis of Variance (ANOVA). This will be an intent-to-treat (ITT) analysis. For our ITT analysis we will analyse our data based on the participants’ original allocation to the groups regardless of any subsequent group changes or participants’ degree of adherence to study protocols or their withdrawal from the study. We will assume data will be missing completely at random (MCAR) in order to enable imputation of missing data using standard techniques. We have postulated a main effect for the experimental condition without an interaction effect. In addition, we intend to use the CD4 T-cell counts and viral loads as objective biological endpoints, with the same statistical procedure being employed. Additional analyses will determine whether the pathway via reduction of alcohol consumption was indeed crucial to the differences in adherence. This can be measured by a cross-lagged panel design, where the alcohol in the time interval before the respective measurement of adherence will be assumed to have a significant effect. Structural equation modelling and path analysis will be used to test this assumption. Models will also be run with ART continuation as the endpoint. More advanced techniques, including generalised estimating equation and multilevel modelling, will also be employed. The association between the biomarker of alcohol consumption and self-reports of alcohol will be analysed using correlation and regression techniques with adjustments for possible confounders. The predictive ability of the biomarker will be assessed using sensitivity and specificity techniques to determine its ability to detect excessive self-reported consumption of alcohol.

#### Analyses for phase 3

Data analysis will be conducted using the same framework approach as described above for Phase 1. We will use the Phase 3 findings to assist with interpreting the findings of the RCT phase.

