## Discussion

We hypothesize that compared to individuals who receive the wellness-focused BI, those who receive the alcohol-focused BI will demonstrate greater reductions in alcohol consumption, and as a result, they will demonstrate higher levels of ART adherence and higher CD4 counts, and will be less likely to have detectable HIV viral loads. This study will indicate whether alcohol-focused interventions are feasible to implement with clinical HIV populations, and also whether they can be used to successfully improve adherence to ART treatment and health-related outcomes among people being treated for their HIV infection.

The proposed study has the potential to advance scientific knowledge in several ways. First, it will be among the first to use a blended MI and PST intervention to target reductions in alcohol use among PLWHA in clinical settings in South Africa. While evidence of the link between alcohol use and poor adherence to ART has led for calls for behavioural interventions to reduce risky drinking among PLWHA, there have been few interventions implemented in clinical settings to address this risk for poor HIV disease outcomes. This study will not only help us answer questions about whether reducing hazardous and harmful alcohol use will lead to improved adherence and HIV disease outcomes but will also provide knowledge about what kinds of behavioural interventions are effective for reducing hazardous/harmful alcohol use among PLWHA in clinical care.

Second, this study hopes to further explain the relationship between alcohol use, ART adherence and HIV disease outcomes. If the proposed intervention is effective, we hope to find that reduced alcohol use facilitates better adherence to ART and consequently improved disease outcomes. This would be a significant contribution to health knowledge and could lead to the development of clinical guidelines for the management of alcohol use among people living with HIV/AIDS. Third, through the employment of alcohol and HIV disease-related biomarkers to assess intervention efficacy, this study will be at the forefront of research conducted in the area of alcohol reduction and ART adherence promotion, and will provide considerable objective data regarding the links between alcohol consumption, ART adherence, and health outcomes.

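### Viral load, measured only at baseline and 12 months, appears to be assigned a repeated-measures group main effect, which would estimate half the intervention effect and would not test the detectability hypothesis

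*Protocol article*

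**What the plan says.** All of the following is in the protocol article.

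- **Procedure.** Under Statistical treatment and analysis of data, Analyses for phase 2: "The hypothesis that alcohol reduction will increase adherence will be tested via a repeated-measures Analysis of Variance (ANOVA"). A few sentences later: "We have postulated a main effect for the experimental condition without an interaction effect". The next sentence names CD4 count and viral load as biological endpoints, "with the same statistical procedure being employed".
- **Other methods in the same paragraph.** It opens by describing the main analysis as "repeated analysis of variance and analysis of covariance, using pre-treatment means and post-treatment means; or two-sample t-tests or chi-squared tests", and later adds: "More advanced techniques, including generalised estimating equation and multilevel modelling, will also be employed".
- **Schedule.** The Follow-Up section lists "viral load (at baseline and 12-month follow-up"), and Table 2 agrees. CD4 count is measured at baseline and at all three follow-ups.
- **Hypothesis.** The Discussion predicts that the alcohol-intervention group "will be less likely to have detectable HIV viral loads". The Abstract lists the secondary outcome as a reduction in viral load, without saying how it is expressed.

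**The concern.** The phrase about the same procedure follows directly after a named test (repeated-measures ANOVA) and a named term (a main effect, no interaction). With one grouping factor and one time factor, the interaction that is ruled out is most naturally group by time. In a randomised trial, however, an intervention effect that is absent at baseline and present afterwards is itself a group-by-time interaction. A main effect that spans baseline dilutes it.

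The dilution is worst for viral load, because half of its observations precede treatment. A real benefit on a named secondary outcome could then be reported as no effect, and any estimate would be about half its true size.

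There is a second mismatch. The Discussion's hypothesis is binary (detectable or not), whereas a repeated-measures ANOVA compares means.

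**Working it through.** **Inputs from the protocol article**

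- Viral load: one value before and one after randomisation (Follow-Up; Table 2).
- Final sample: 300, 150 and 150 in the alcohol, wellness and usual-treatment arms. With the stated 20% attrition, 300 × 0.8 = 240 and 150 × 0.8 = 120.
- Two-sided 5% level; within-subject correlation ρ = 0.7, given for the drinking outcome only.

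The article gives no power or effect size for viral load, so there is no figure of its own to reproduce on this point.

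**Assumptions**

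- Equal variance σ² at both visits and in both arms.
- ρ from 0.3 to 0.7, because no value is given for viral load.
- The 12-month effect δ is set so that baseline-adjusted analysis of covariance has 90% power.

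**Step 1: what the main effect estimates.** With two occasions, the group main effect is the between-arm difference in (baseline + 12 months)/2. Randomisation makes the expected baseline difference zero, so its expected value is (0 + δ)/2 = δ/2.

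**Step 2: standard errors.** Write S = √(1/n₁ + 1/n₂).

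- Main effect: σS√((1+ρ)/2)
- Analysis of covariance at 12 months: σS√(1−ρ²)
- Change from baseline (group by time): σS√(2(1−ρ))

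**Step 3: ratio of test statistics.** For 90% power, δ = (1.960 + 1.282)σS√(1−ρ²), so the analysis of covariance has an expected z of 3.242. Dividing δ/2 by the main-effect standard error gives 3.242 × √((1−ρ)/2). Sample size and σ cancel. The sample-size multiple needed to recover 90% power is 2/(1−ρ).

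| ρ | Expected z, main effect | Power, main effect | Power, group by time | Power, analysis of covariance | Sample-size multiple |
|---|---|---|---|---|---|
| 0.7 | 3.242 × √0.15 = 1.26 | 24% | 85% | 90% | 6.7 |
| 0.5 | 3.242 × √0.25 = 1.62 | 37% | 80% | 90% | 4.0 |
| 0.3 | 3.242 × √0.35 = 1.92 | 48% | 74% | 90% | 2.9 |

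**Step 4: simulation check.** With 4,000 simulated trials of 240 v 120 at ρ = 0.7 and a true 12-month reduction of 0.259 SD, the mean main-effect estimate was a reduction of 0.129 SD. Power was 23.8% for the main effect and 89.5% for analysis of covariance.

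**Step 5: CD4.** With one baseline and three follow-up values and a constant effect δ after baseline, the main effect estimates (0 + δ + δ + δ)/4 = 0.75δ. The fault is the same but milder.

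**Step 6: hypothesis against test.** The Discussion asks whether fewer participants are detectable. The main effect asks whether mean viral load, averaged over baseline and 12 months, differs. A result on the second does not answer the first.

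**The case against.** The strongest reply is that the text does not fix the reading. The paragraph opens with analysis of covariance, t-tests and chi-squared tests, and adds generalised estimating equations and multilevel models. The sample size section works by analysis of covariance and mentions power for a possible interaction of between- and within-subject factors. Analysis of covariance with baseline as covariate does not halve the effect, and a main effect without an interaction could then mean a constant effect over follow-up. A chi-squared test of detectability at 12 months would address the Discussion's hypothesis directly.

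Most of this stands. A reader might infer that the plan definitely commits viral load to the diluted test; the document supports only that this is the most natural reading. The reply does not remove the point, because none of the sound methods is assigned to viral load. The only sentence that assigns a method refers back to the repeated-measures ANOVA. A list under which the same data could be tested with 24% or 90% power also needs to be settled in advance.

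A reader might also infer that viral load would be analysed on the wrong scale, as untransformed copies. The document names no scale, and transformation and values below the assay limit are commonly left to an SAP, so that is not part of this point. Nor does the document rank viral load as the leading objective HIV outcome: it is one of several secondary outcomes and is named alongside CD4 count.

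**Conclusion.** The concern holds in conditional form. If the wording is followed as it most naturally reads, with baseline as a level of the repeated factor, the viral-load test estimates exactly half the 12-month effect. It has about 24% to 48% power (ρ from 0.7 to 0.3) where a baseline-adjusted comparison has 90%.

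The halving needs only randomisation and the two-visit schedule. The powers also need equal variances and the assumed range of ρ. They describe the cost of this test relative to a better one, not the power the trial will have for viral load, which cannot be derived from the document.

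Separately, and whatever ρ is, an ANOVA of mean viral load does not test the detectability hypothesis in the Discussion. The wording should be corrected before analysis.

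**What to change.** In Analyses for phase 2, replace the reference to the same procedure as follows.

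- **Viral load:** compare between arms the proportion with detectable viral load at 12 months, adjusted for baseline detectability and for site (the randomisation stratum). Add 12-month viral load adjusted for its baseline value as a supporting analysis. The exact model and the handling of values below the assay limit can be left to the SAP.
- **CD4 count:** compare follow-up values between arms with baseline as a covariate, not as a level of the repeated factor.
- **Outcome statement:** word the viral-load outcome in the Abstract and the hypothesis in the Discussion so that they name the same quantity.

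The cost is wording only. Every measurement needed is already scheduled, and neither sample size nor visits change.

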## Background

The consumption of alcohol has been closely investigated within the context of HIV [1]. Data suggests that hazardous alcohol use directly contributes to the acquisition and transmission of HIV as well as to antiretroviral therapy (ART) non-adherence, the worsening of HIV disease, progression to AIDS, and mortality [2–4]. Not only does South Africa have high numbers of persons who are HIV positive and on ART, but it also has one of the highest levels of per capita alcohol consumption *per drinker* globally and one of the highest levels of heavy episodic drinking globally among men and women [5].

ART is essential for improving and maintaining physical health, reducing HIV viral load, and reducing morbidity and mortality among people living with HIV and AIDS (PLWHA) [6]. Sub-optimal adherence to ART regimens can result in the development of resistance to ART, and ultimately poorer treatment outcomes, and mortality [7–10]. Alcohol consumption is a concern in relation to ART as alcohol may impact the cognitive processes necessary to maintain adequate adherence [11]. Furthermore, beliefs that ART medications should not be taken while consuming alcohol may cause drinkers to fail to adhere to treatment [12–15]. Hendershot et al.’s meta-analysis found that drinkers were 50%-60% as likely to be adherent as non-drinkers [16]. This effect was amplified for problem drinkers, who were only 47% as likely to be adherent as non-problem drinkers or abstainers. In addition, missed ART doses occur primarily on drinking days [17]. In keeping with these findings, the consumption of alcohol has been shown to be significantly associated with time to ART treatment failure as well as subsequent survival [18].

At a molecular level, in vitro experiments have demonstrated that exposure to even a moderate dose of alcohol can increase HIV replication in peripheral blood mononuclear cells [19]. Evidence suggests that alcohol use may lead to an increase in HIV viral replication in those infected with HIV [19–23]. Alcohol consumption may also impact CD4 cells, with research demonstrating lower CD4 counts among heavy alcohol users [24–26].

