The overall goal of this project is to improve knowledge on the efficacy of an alcohol reduction intervention on alcohol consumption among PLWHA on ART, ART adherence and HIV treatment outcomes. The study has the following specific aims:(i)*To adapt a blended MI and PST intervention to address harmful/hazardous alcohol use in HIV positive populations in Tshwane, South Africa*.(ii)*To assess the efficacy of the blended MI-PST alcohol-focused intervention for reducing the average volume of alcohol consumed, improving ART adherence, maintaining ART adherence, improving HIV treatment continuation, and reducing disease progression relative to an equal-attention wellness intervention and treatment as usual (TAU) control group*. We hypothesise that those patients who receive the MI-PST alcohol-focused intervention will be more likely than those in the wellness intervention or TAU control groups to reduce their volume of alcohol consumption (our primary outcome) and that the participants in the alcohol-reduction intervention who reduce their alcohol consumption will have significantly greater improvements in their degree of ART adherence and in their HIV disease-related outcomes (including their treatment continuation and the progression of their disease) relative to participants in the wellness intervention or control group.(iii)*To qualitatively assess counsellors’ and participants’ subjective responses to the blended MI-PST intervention*.

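### The pathway question is about mediation, but the only criterion named is that earlier drinking predicts later adherence, a path that does not involve randomised arm

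*Protocol article*

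**What the plan says.** The subsection on phase 2 analyses in the protocol article sets the question: "Additional analyses will determine whether the pathway via reduction of alcohol consumption was indeed crucial to the differences in adherence". It then gives the means of answering it: "This can be measured by a cross-lagged panel design, where the alcohol in the time interval before the respective measurement of adherence will be assumed". What is assumed there is that this lagged effect is significant. The next sentence says what the modelling is for: "Structural equation modelling and path analysis will be used to test this assumption".

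Adherence itself is handled separately: "The hypothesis that alcohol reduction will increase adherence will be tested via a repeated-measures Analysis of Variance (ANOVA"), analysed by intention to treat. The aims give the causal chain behind this, expecting that "participants in the alcohol-reduction intervention who reduce their alcohol consumption will have significantly greater improvements in their degree of ART adherence". The Discussion repeats the chain for the comparison with the wellness arm. The Background cites a meta-analysis in which "drinkers were 50%-60% as likely to be adherent as non-drinkers", and problem drinkers were "only 47% as likely to be adherent as non-problem drinkers or abstainers".

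**The concern.** Whether drinking carried the between-arm differences is a mediation question. It needs two links: arm changes alcohol, and that change in alcohol changes adherence. The stated criterion examines only the second. Randomised arm, the arm-to-alcohol path, an indirect effect and a remaining direct effect are not part of it.

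There is a second weakness. A standard cross-lagged coefficient mixes change within a person with stable differences between people. If people who habitually drink more also habitually adhere less, the coefficient can be significant even though changing one's drinking does nothing for adherence.

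At stake is a prominent causal claim. The article presents reduced drinking as the route to better adherence and disease outcomes, and says such a finding could inform clinical guidelines. Read as written, the criterion could support that claim when an adherence gain came by another route, such as the education on alcohol and HIV listed in Table 1.

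**Working it through.** **1. Question against criterion.** Write a for the effect of arm on alcohol and b for the effect of alcohol on later adherence. The null for the stated question is a × b = 0. The null for the named test is b = 0. They differ whenever a = 0 and b is not 0. The article gives no figure for this analysis, so there is none to reproduce.

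**2. Inputs from the sample size section.**
- Completers: 600 × (1 - 0.20) = 480, of whom 240 are in the alcohol arm.
- One baseline and three follow-up measures, within-subject correlation 0.7, two-sided 5%.
- Planning effect on drinking: (4.75 - 3.58) / √((1.81² + 3.22²)/2) = 1.17 / 2.61 = 0.45 SD.

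**3. Assumed inputs.** Path sizes and the trait correlation are not in the article. One anchor reads the Background's 47% as an odds ratio: d = ln(0.47) × √3/π = -0.42, and r = d/√(d² + 4) = -0.20. Because that figure compares problem drinkers with others, a range is shown.

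**4. Trait model.** Alcohol and adherence are correlated stable traits plus occasion noise. Adherence is regressed on previous adherence, previous alcohol and visit, with standard errors clustered by person.

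| Truth | Trait correlation | Lagged path significant |
|---|---|---|
| a = 0, b = 0 | 0 | about 5% |
| a = 0, b = 0 | -0.1 | 25% |
| a = 0, b = 0 | -0.2 | about 74% |
| a = 0, b = 0 | -0.3 | 97% |

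With a = 0 and b = -0.10 the lagged path is significant in 97-100% of trials, while a product test that includes arm rejects in about 1-5%. Another build of this model, with no trait correlation, gave 73-100% for b from -0.10 to -0.30.

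**5. Autoregressive model.** This is a separate construction: alcohol autoregression 0.7, adherence autoregression 0.5 (assumed), arm included as a covariate, significance counted in the predicted direction only.

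| Size of b | Lagged path, a = 0 | Lagged path, a = 0.45 SD | Both paths required, a = 0 |
|---|---|---|---|
| 0.05 | 60% | 60% | 1.3% |
| 0.10 | 99% | 99% | 2.8% |
| 0.15 | 100% | 100% | 2.5% |
| 0.20 | 100% | 100% | 3.1% |

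The second and third columns are equal, so the lagged path carries no information on whether the intervention changed drinking. With b = 0 and a = 0, an assumed shared trait (loading 0.3 to 0.5) gives 15-57%; with no shared trait the rate is about 3%.

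**6. When the arm does change drinking (a = -0.45 SD) but b = 0.** Trait correlation is -0.2 to -0.3 unless stated.
- Lagged path read together with the arm-to-alcohol test: 71% false support at -0.2.
- Product of paths adjusted for baseline covariates: 13-24%.
- Product of paths with an ordinary random intercept: about 71-98%.
- Product of paths on change from baseline: about 5%.

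**The case against.** The strongest defence is that nothing in the article says the pathway will be declared from the lagged coefficient alone. Structural equation models usually estimate direct and indirect effects, and the unseen analysis plan may include arm. That is possible. But the article does more than stay silent: it states the question, names a path, and says the modelling will test that path. A plan that followed this text would inherit the mismatch.

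The second defence is that the missing link is tested elsewhere. Arm on alcohol is the primary outcome, so a failure to change drinking would be visible. Reading the lagged path together with that test brings false support down to 3.6% (no path) and 5.2% (path -0.20) at a trait correlation of -0.2 when the arm does nothing to drinking. This stands, and it limits the damage. The plan does not tie the two results together, however, and combining them does not remove trait confounding when the arm works (71%).

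A reader might also infer two stronger things that the documents do not support.
- That the pathway would be confirmed almost regardless of the truth. It would not: some alcohol-adherence association is needed, and the rate falls to about 5% with neither a path nor a trait correlation, and to 60% at a path of 0.05.
- That the Background already treats that association as established in this population. Its figures compare drinkers with non-drinkers, and problem drinkers with others. This trial enrols only weekly heavy drinkers scoring no more than 22 on the AUDIT, so the association may be weaker.

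Finally, the wellness arm also uses motivational interviewing and problem solving with equal attention. Against that arm, general counselling and problem-solving skills are a poor rival explanation; the alcohol-specific HIV education still differs.

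**Conclusion.** The point holds as a mismatch between the stated question and the stated criterion. A significant effect of earlier drinking on later adherence does not show that the adherence differences between arms came through reduced drinking.

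The size is conditional. Where a real path of about 0.10 exists, the criterion is met in nearly every trial whether or not the intervention changed drinking. Where no path exists, it is met in about 5% to 74% of trials as the assumed trait correlation goes from 0 to -0.2. All these rates rest on assumed path sizes, trait correlations and model structure.

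The primary comparison is untouched, and these are additional analyses of a secondary outcome. The change is still worth making because the causal claim is prominent in the aims and Discussion.

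**What to change.** Replace the criterion, and delete the clause under which the lagged effect is assumed to be significant. Suggested text:

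> Mediation will be tested as the indirect effect of randomised arm on adherence at 6 and 12 months through alcohol consumption at the preceding visit, for alcohol v wellness and for alcohol v TAU. It will be the product of the arm-to-alcohol and alcohol-to-adherence paths with a bootstrap 95% CI, in a model that keeps a direct effect of arm. The alcohol-to-adherence path will be estimated within person. The pathway is supported only if the interval excludes zero. A significant alcohol-to-adherence path alone will not be taken as evidence of mediation.

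Name one within-person form in advance: change from baseline, person-mean centring, or a random-intercept cross-lagged model with correlated intercepts. An ordinary random intercept alone is not enough (step 6 of the working).

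The cost is wording only: alcohol and adherence are already to be measured at all four visits and structural equation modelling is already planned. The claim becomes harder to make, and power is lower for small paths. The change-from-baseline form kept 91-100% power in one simulation (arm effect -0.45 SD, paths -0.15 to -0.30), but this depends on how baseline adherence arose. If it does not yet reflect earlier drinking, and occasion noise has variance s² at each visit, regressing on change in alcohol estimates b × s²/(2s²) = b/2, so power falls. The result would still rest on no unmeasured time-varying confounding of alcohol and adherence, which should be stated with a sensitivity analysis.
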